### Randomization

Allocation will be performed by clusters, and the randomizing unit will be the teaching units. The analysis unit will be the residents. Randomization will be performed by using the Epidat 4.1 software module to assign patients' treatments. The intervention "e-learning EDUCAGUIA" will be regarded as the treatment, and the routine CPG dissemination system will be used as a control variable. To obtain the same number of centers

in both the intervention and control groups, the option of balanced groups will be chosen.

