### Recruitment

All Spanish teaching units will be contacted by mail offering participation via an agreement form to participate in the EDUCAGUIA study. TUFCM agreeing to participate to the study will be randomly assigned to one of the two groups: the intervention or the control group.

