### Sample size

The sample size has been calculated considering a relevant post-intervention average difference of 10 points on a 100-point evaluation questionnaire between groups and a standard deviation of 0.5 [31]. Assuming an alpha error of 0.05 and a beta error of 0.10, 84 subjects are required for each group. Because randomization is performed by clusters, the sample size has been adjusted to take into account the design effect. Thus, for an average of 30 residents per teaching unit, and an intraclass correlation coefficient (ICC) of 0.03 (literature shows an ICC of 0–0.052 for similar teaching interventions) [32], a design effect of 1.87 has been obtained. With these assumptions, and expecting a 25 % loss to follow-up after a 6-month period, the required sample size is 394 (197 per group).

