| d             | Request to Access to training on Educational Games DEMO online by email                                                                                                                                                           |
| 2             | Use of the e-learning EDUCAGUIA application. One month accesible                                                                                                                                                                  |
| e             | GPC recommendations postintervention Competence Test . Outcomes 1 and 6 months.                                                                                                                                                   |

**Fig. 2** Complex intervention pat plot. e-EDUCAGUIA

the last three contests; a teaching plan that includes training on EBM/CPG in the unit; and the number of EBM/CPG training hours in the past year

(b) Resident doctor variables

- Sociodemographic: age, sex, nationality, residency year
- Position in the national exams to access specialty (MIR number); grades obtained in R-1 and R-2 residency years (apt, outstanding, excellent); completion of other specialties; year of obtaining a university degree in medicine; and PhD (yes/no)
- Training: specific training on EBM in the past 5 years and corresponding hours of training, training on critical reading capabilities and corresponding hours of training, having attended formative sessions on how to use CPGs, and corresponding hours of training
- Other variables to achieve secondary objectives: adherence to CPGs, measured as time spent using the application.

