### Discussion

Teaching units from across Spain will participate in this clinical trial, which anticipates high external outcome validity. Additionally, this intervention might provide information to consider for training in other specialties.

The intervention to be assessed cannot be masked, which could influence its effect. Because there is a possibility of contamination bias among residents, randomization by clusters has been proposed, under the assumption that the number of clusters will be sufficient for each group. Geographic dispersion of the teaching units reduces the possibility of contamination.

Teaching strategies are complex interventions; the design of educational games as an interactive, self-learning application allows for standardization of the intervention.

The considerable variability foreseen between teaching units regarding training in CPGs could imply that some residents have better training with some of these CPGs, which could result in a lack of improvement in these residents' decision-making scores (competency test score). However, this possibility will be adjusted using the training variables of both the teaching units and the residents.

To evaluate the intervention's effectiveness, the primary measurement will take place 1 month after implementation; at this time, our primary objective will be to confirm the effectiveness of the e-learning EDUCAGUIA strategy as a learning tool. Its effect at 6 months after the intervention might not remain, which would lead to a study on the effectiveness of reinforcement interventions. Measuring the primary response at 6 months was considered an option, but the characteristics of training during residency periods make it possible for the residents to acquire the knowledge and abilities of the intervention during rotations or other courses within that time period, thus hindering the isolation of the intervention effect.

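### Allocation equalises only the number of teaching units per arm, leaving an avoidable risk of a material chance imbalance in unit guideline training or size

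*Protocol*

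**What the plan says.** The Protocol's Randomization section states: "Allocation will be performed by clusters, and the randomizing unit will be the teaching units". It uses a software option whose stated purpose is an equal number of centres: "in both the intervention and control groups, the option of balanced groups will be chosen". It names no stratification, matching, minimisation or covariate constraint. Under Recruitment all Spanish units are approached, and "TUFCM agreeing to participate to the study will be randomly assigned to one of the two groups". No target or maximum number of units is given.

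The Sample size section works "for an average of 30 residents per teaching unit" and arrives at 394 residents, 197 per arm.

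The Discussion expects the units to differ: "The considerable variability foreseen between teaching units regarding training in CPGs could imply that some residents have better training". It says this will be handled by adjusting for the training variables of units and residents.

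The unit characteristics listed under Variables include the number of residents in each training year, "a teaching plan that includes training on EBM/CPG in the unit", and hours of such training in the past year. Fig. 2 places the unit and resident baseline variables, and the baseline competence test, above the randomisation row.

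**The concern.** Equal unit counts do not make the arms alike when units are few and dissimilar. Prior guideline training is a factor the Protocol itself expects to influence the competence score. If it falls unevenly between arms, the observed contrast mixes the effect of the games with a difference between units. If large units fall mostly in one arm, the planned 197 per arm will not be met even with equal unit counts.

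The information needed to limit both problems is due to be collected before allocation, but the allocation does not use it. The remedy offered is adjustment in the analysis. With about 14 units there are only about 12 between-unit degrees of freedom (14 units less 2 arms), so few unit-level covariates can be fitted. Adjustment also works least well when a factor is nearly aligned with arm.

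**Working it through.** **Reproducing the plan's sample size.** The inputs are from the Sample size section. The stated SD of 0.5 gives 84 per arm only if it is read as a standardised difference of 0.5, that is, 10 points with an SD of about 20.

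- n per arm = 2(1.960 + 1.282)²/0.5² = 84.1 (stated: 84).
- Design effect = 1 + (30 − 1) × 0.03 = 1.87, as stated: "a design effect of 1.87 has been obtained".
- 84 × 1.87 = 157.08, and 157.08 × 1.25 = 196.35, so 197 per arm and 394 in total, as stated.

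**Number of units.** 394/30 = 13.1. Per arm, 197/30 = 6.6, rounded up to 7, so about 14 units. The count rests on an average of 30 participating residents per unit.

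**A binary unit factor.** Assume that k of 14 units have an EBM/CPG teaching plan. There are C(14,7) = 3432 equally likely 7:7 allocations.

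- k = 7, 5–2 or worse: 2 × (1 + 49 + 441)/3432 = 982/3432 = 28.6%.
- k = 7, 6–1 or worse: 2 × (1 + 49)/3432 = 100/3432 = 2.9%.
- k = 6, 5–1 or worse: 2 × (8 + 168)/3432 = 352/3432 = 10.3%.
- k = 5, 4–1 or worse: 2 × (36 + 420)/3432 = 912/3432 = 26.6%.

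The documents do not give k.

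**A continuous unit factor.** The standardised difference between arms has standard error √(2/m) with m units per arm. The probability of a difference above 0.5 SD is 2[1 − Φ(0.5/√(2/m))].

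| Units per arm | SE | Above 0.5 SD | Above 1 SD |
|---|---|---|---|
| 7 | 0.535 | 35% | 6% |
| 10 | 0.447 | 26% | 2.5% |
| 15 | 0.365 | 17% | 0.6% |

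Enumerating all 3432 allocations over simulated normal covariates gives 37% and 6% for 7 per arm. For at least one of two independent factors it gives about 60% (above 0.5 SD) and 11% (above 1 SD).

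**Unit size.** The Protocol gives only a mean. Simulating 14 units with gamma-distributed sizes of mean 30, the probability that one arm is more than 1.5 times the other is 1%, 13%, 25% and 35% for an assumed coefficient of variation of 0.3, 0.5, 0.65 and 0.8.

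**Effect on the score.** The between-unit SD is 20 × √ICC, and its contribution to the standard error of the arm difference is that SD × √(2/7). The upper ICC is the top of the Protocol's cited range ("literature shows an ICC of 0–0.052 for similar teaching interventions").

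- ICC 0.03: SD 3.5 points, SE 3.46 × 0.535 = 1.9 points.
- ICC 0.052: SD 4.6 points, SE 4.56 × 0.535 = 2.4 points.

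As an extreme case, let the teaching plan (7 of 14 units) explain all between-unit variance at ICC 0.03. Units with and without a plan then differ by 2 × 3.46 = 6.9 points. A 5–2 split shifts the unadjusted contrast by (5/7 − 2/7) × 6.9 = 3.0 points.

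**After constraint.** If allocation is drawn only from the best-balanced 10% of the 3432 allocations on two simulated covariates, the probability of a difference above 0.5 SD in either falls from about 60% to about 0%.

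**The case against.** Equal-count cluster randomisation is a valid, unbiased design, and nothing in the Randomization section is wrong or contradictory. Chance differences between randomised units are what the design effect and the two-level model are there to absorb. The Protocol also plans to adjust for training, partly through resident-level variables that do not use between-unit degrees of freedom. The 14 units are not a planned number: no cap is stated, and partial participation would require more units. A 60:40 split of residents keeps 4 × 0.6 × 0.4 = 96% of the efficiency of an equal split at resident level.

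Most of this stands, and it limits the point. A reader might infer that a serious imbalance is likely. The figures do not support that: 6–1 or worse has probability 2.9% under the assumed prevalence, and a difference above 1 SD in a given factor about 6%. Only the moderate 0.5 SD threshold, applied to either of two assumed independent factors, passes one half. A reader might also infer that the treatment comparison is biased. It is not; the expected imbalance is zero.

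The objection does not show that the risk should be accepted. The promise to adjust for training appears in the Discussion, while the Statistical analysis section lists a Student's t test and a two-level model without naming covariates. A covariate list could properly be left to an SAP, but the allocation method is fixed here. Unit size is not named for adjustment. Balancing at allocation adds precision and credibility that later adjustment only partly recovers.

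**Conclusion.** The point holds as a cheap improvement to the design, not as an error. With about 7 units per arm, a material chance imbalance (above 0.5 SD) in a given unit factor has a probability of about 35–37%, falling to about 17% with 15 per arm. The cost is in precision and interpretability. Its scale is a standard error of about 1.9–2.4 points against the 10-point target, which a correct cluster analysis carries in its interval.

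These sizes rest on four assumptions: the inferred 14 units, a score SD of about 20, the Protocol's ICC range, and assumed distributions of teaching plan and unit size. Three things are firm: allocation balances only unit counts, the Protocol expects units to differ in guideline training, and the relevant unit data are scheduled before randomisation.

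**What to change.** In the Randomization section, state that all agreeing units are allocated at one time, after the unit baseline data are in. Use covariate-constrained randomisation with equal unit counts, constraining on EBM/CPG teaching plan (or training hours) and on the number of third- and fourth-year residents. Give the balance criterion and the share of allocations retained. With 14 units, the best 10% of 3432 still leaves about 343 allocations to draw from.

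A simpler alternative is to stratify on the teaching plan alone. If 7 units have a plan, the split is then held to 4–3, provided the odd units in the two strata are offset so that the arms stay 7:7. Crossing teaching plan with size is not advisable: four strata average 14/4 = 3.5 units, and odd-sized strata could break the equal counts the section now secures.

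Name the constraining factors as fixed effects in the mixed model in the Statistical analysis section, and state the expected number of units.

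The cost is that every unit must be recruited before any is allocated, and one or two of about 12 between-unit degrees of freedom are used. No additional residents are needed, and no data beyond those already listed under Variables.

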### Intervention

Both groups will attend an initial 60-min session comprising the following content: CPGs—what they are and where to find them; information on and presentation of the GuiaSalud website and a link to the guidelines library; and instructions for downloading guidelines.

### For the control group

Routine dissemination of clinical guidelines will be sent via e-mail. The link to the CPGs from the GuiaSalud website will be provided.

### For the e-EDUCAGUIA intervention group

The e-learning EDUCAGUIA is a complex intervention that combines several components based on an educational game with a ranking and a competitive combination of game styles. It has been designed by a multidisciplinary team of primary healthcare professionals with experience in training students and residents, elaborating CPGs and developing new technologies as teaching tools. After routine disseminations of clinical guidelines via e-mail, as in the control group, residents belonging to the teaching units allocated in this intervention arm will be invited to access the educational games' online training demo by e-mail. They will then have access to the e-learning EDUCAGUIA application software for one month.

Each guideline comprises different clinical scenarios related to several recommendation areas, each encompassing five dimensions (e.g., diagnosis, treatment, referral, information, and patient health education). The application will generate a report for each "game" or training session completed by the residents and will rank them accordingly to enable comparisons with the rest of the guideline users. Figure 2 shows the various components of both the control and the e-EDUCAGUIA intervention groups [33, 34].

### Competence assessment in both groups

An evaluation of baseline competence will be performed for each guideline prior to its presentation, and two further tests will be carried out at 1 and 6 months after the intervention. The test will evaluate the level of knowledge and decision-making in relation to ten hypothetical cases of routine clinical practice that are related to the content of each guideline; the test will yield a maximum score of 100 and will be completed within 45 min.

### Variables

The primary outcome variable will be the participant score obtained in the test assessing competence 1 month after the intervention. The secondary outcome variable

[figure not shown]

will be the competence test score 6 months after the intervention.

(a) Teaching unit variables

- Sociodemographic characteristics of the program director and technician: sex, age, specialty,

academic level, time spent in that position, experience in elaborating guidelines or recommendation, and training in EBM

- Unit characteristics: total number of residents (R1, R2, R3, R4); position of the teaching unit in the ranking, obtaining residency positions in

[figure not shown]

|               |                                                                                                                                                                                                                                   |
|---------------|-----------------------------------------------------------------------------------------------------------------------------------------------------------------------------------------------------------------------------------|
| 1             | Initial 60-minute session comprising the following content: Clinical Practice Guideline; information on and presentation of the GuiaSalud website, and a link to the guidelines library; instructions for downloading guidelines. |
| a             | Family Medicine Teaching Units and Residents Doctors baseline variables                                                                                                                                                           |
| b             | CPG Recommendations Baseline Competence Test                                                                                                                                                                                      |
| RANDOMIZATION |                                                                                                                                                                                                                                   |
| c             | Routine dissemination of CPG recommendations by mail.                                                                                                                                                                             |
| d             | Request to Access to training on Educational Games DEMO online by email                                                                                                                                                           |
| 2             | Use of the e-learning EDUCAGUIA application. One month accesible                                                                                                                                                                  |
| e             | GPC recommendations postintervention Competence Test . Outcomes 1 and 6 months.                                                                                                                                                   |

**Fig. 2** Complex intervention pat plot. e-EDUCAGUIA

the last three contests; a teaching plan that includes training on EBM/CPG in the unit; and the number of EBM/CPG training hours in the past year

(b) Resident doctor variables

- Sociodemographic: age, sex, nationality, residency year
- Position in the national exams to access specialty (MIR number); grades obtained in R-1 and R-2 residency years (apt, outstanding, excellent); completion of other specialties; year of obtaining a university degree in medicine; and PhD (yes/no)
- Training: specific training on EBM in the past 5 years and corresponding hours of training, training on critical reading capabilities and corresponding hours of training, having attended formative sessions on how to use CPGs, and corresponding hours of training
- Other variables to achieve secondary objectives: adherence to CPGs, measured as time spent using the application.

**All variables will be collected in an electronic case report form**

For secondary objective 3, each teaching unit and mentor will receive an e-mail containing information on the project and inviting them to complete the survey with the link included. The questionnaire has been developed by the research team.

For secondary objective 4, a study using a qualitative methodology was performed in a phase prior to the beginning of the trial, including discussion groups that studied the barriers and facilitators in the use of CPGs. Using the results from that study, along with the questionnaire developed by Sola et al. [35] for Spanish doctors, a new questionnaire will be created that will be sent to the family medicine residents by the teaching units.

**Statistical analysis**

1. Descriptive and exploratory analysis: This analysis will include participants' baseline characteristics and outcomes, means and standard deviations (SD) for

continuous variables, and proportions for categorical variables with its corresponding 95 % confidence interval (CI). Baseline comparison between the two groups in terms of the score competence test and descriptive and prognostic factors will be performed by bi-variant statistical tests.

2. Inferential analysis: Student's *t* test with a 95 % CI will be performed to compare both groups' results in the competence test in terms of score at baseline and 1- and 6-month post-implementation of each CPG recommendation.
3. Multilevel analysis: a mixed model will be constructed for the evaluation of the influence of the teaching unit on the effectiveness of the intervention. The dependent variable will be the score obtained in the competence test. The model will consist of two levels: resident doctors will comprise the first level and the teaching unit will comprise the second.
4. Dropouts and missing data

Because this trial will use an online system to allocate participants and collect baseline and outcome data, participants can leave the study at any time. To minimize the possibility of dropouts and missing data, several strategies will be considered. If a participant leaves the study before randomization, the participant will be excluded and we will not consider this as missing participant data.

All statistical tests will be performed with an intention-to-treat analysis. The last observation carried forward will be used for missing data imputation, and there will be report analyses with and without imputation [36].

Significance will be set at  $p < .05$ . Calculations will be performed using MLwiN and STATA v.12 software with specific related modules.

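### The protocol fixes unadjusted t tests at 1 and 6 months and tests the baseline competence score for group differences, but does not name that score as a covariate

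*Protocol*

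**What the plan says.** **Collection.** Under Competence assessment in both groups, the protocol says "An evaluation of baseline competence will be performed for each guideline prior to its presentation". Further tests follow at 1 and 6 months, and the test has a maximum score of 100. The key to Fig. 2 lists the baseline test above the randomisation row. The score is therefore a pre-allocation measurement of the same construct as the outcome.

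**Use.** The Statistical analysis section does four things that bear on this score:
- Item 1: "Baseline comparison between the two groups in terms of the score competence test and descriptive and prognostic factors will be performed by bi-variant statistical tests".
- Item 2, the inferential analysis: Student's t tests between groups at baseline, 1 month and 6 months. No adjustment is mentioned.
- Item 3: a two-level mixed model, residents within teaching units, built to evaluate the influence of the unit. It says "The dependent variable will be the score obtained in the competence test" and lists no covariates.
- Item 4: last observation carried forward for missing data, with results reported with and without imputation.

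**Adjustment mentioned elsewhere.** The Abstract refers to a linear multilevel regression for adjustment without naming covariates. The Discussion expects units to differ considerably in guideline training and says "this possibility will be adjusted using the training variables of both the teaching units and the residents".

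**The concern.** A baseline measurement of the outcome is usually a useful covariate, and here it is already being collected. The plan instead puts it through significance tests. In a properly randomised trial such a test examines a null hypothesis known to be true; its p-value neither measures nor removes the effect of an imbalance on the treatment estimate.

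The named between-group comparison then uses raw follow-up scores. Two things are at stake. The effect is estimated with more variance than necessary. And in the single allocation that actually occurs, part of any chance difference in baseline competence is read as intervention effect. Chance differences are not negligible when whole teaching units are allocated and the planning figures imply few of them. The Discussion itself expects units to differ.

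**Working it through.** **Inputs from the Sample size section**
- "Assuming an alpha error of 0.05 and a beta error of 0.10, 84 subjects are required for each group", for a "relevant post-intervention average difference of 10 points on a 100-point evaluation questionnaire between groups".
- The spread is printed as "a standard deviation of 0.5".
- 30 residents per unit, ICC 0.03, design effect 1.87, 25% loss, 197 per group (394 in total).

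**Reproducing the plan's figures**
- Two-sided alpha 0.05, power 0.90, standardised difference 0.5: n = 2 × ((1.960 + 1.282)/0.5)² = 84.06, against 84 stated.
- Taken literally, an SD of 0.5 points gives n = 1 per group. So 84 requires 0.5 to be the standardised difference, which makes the SD 10/0.5 = 20 points. This SD is inferred.
- Design effect: 1 + 29 × 0.03 = 1.87.
- 84 × 1.87 = 157.08; × 1.25 = 196.35, rounded up to 197 per group.
- Number of units: 394/30 = 13.1, so about 13 to 14. This is inferred; the protocol gives no number.

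**Chance imbalance at baseline** (197 per group)
- SE = 20 × √(2 × 1.87/197) = 2.76 points; 95% range ±5.4 points.
- Probability of a difference of 5 points or more in either direction: about 7%.
- Over the protocol's quoted ICC range the SE is 2.02 points (ICC 0) to 3.19 points (ICC 0.052).
- With similar spread at both times, an unadjusted comparison carries about r times the imbalance. For 5 points that is 5 × 0.3 = 1.5 to 5 × 0.6 = 3.0 points.

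**Precision of the 1-month effect**
- Effective n per group after loss: 197 × 0.75/1.87 = 79.0.
- Cluster-adjusted SE, no covariate: 20 × √(2/79.0) = 3.18 points.
- The baseline-to-follow-up correlation r is not in the protocol. The values 0.3, 0.5 and 0.6 are assumptions.

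A. *Same r at unit and resident level*: variance is multiplied by 1 − r².

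B. *Baseline explains only within-unit variance*: the within-unit share of the variance is (1 − 0.03)/1.87 = 0.519, so variance is multiplied by 1 − 0.519 r².

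| r | Variance reduction, A | SE, A | Variance reduction, B | SE, B |
|---|---|---|---|---|
| 0.3 | 9% | 3.04 | about 5% | 3.11 |
| 0.5 | 25% | 2.76 | about 13% | 2.97 |
| 0.6 | 36% | 2.55 | about 19% | 2.87 |

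**Power for 10 points under A**
- Normal approximation, Φ(10/SE − 1.96): Φ(3.14 − 1.96) = 88% unadjusted; 91%, 95%, 98% adjusted.
- Non-central t with 14 − 2 = 12 degrees of freedom (critical value 2.18): 82% unadjusted; 86%, 91%, 95% adjusted.

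**Power for 10 points under B**
- Normal approximation: 90%, 92%, 94%.
- t with 12 degrees of freedom: 84%, 87%, 89%.

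**The case against.** **The covariates are left open.** Item 3 gives no covariate list, the Abstract speaks of adjustment, and a statistical analysis plan that is not shown may list covariates. This stands as far as it goes: a reader might infer that baseline adjustment is ruled out, and the protocol does not say that. But the point does not rest on silence alone. The protocol positively specifies baseline significance tests and unadjusted t tests, and a covariate list for item 3 would leave items 1 and 2 as they are.

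**The score is not confined to baseline tests.** A reader might infer that it is. It is also described, and under last observation carried forward a resident who misses the 1-month test contributes the baseline score as the outcome. That is a use, though one that passes an imbalance into the outcome in full for those residents.

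**Imbalance is not wholly uncorrected.** The Discussion's adjustment for training variables may remove part of a between-unit difference. This stands, although the Statistical analysis section does not carry that promise forward. The protocol gives no correlation for any predictor, so it cannot be shown that the baseline score is the strongest one.

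**Omitting the covariate is not bias.** Correct: averaged over allocations, the raw comparison is unbiased. The loss is in precision and in protection against imbalance in the one allocation made.

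**The t test's printed interval would not be too wide.** Also correct. A plain t test with 148 per group and SD 20 reports an SE near 20 × √(2/148) = 2.32, below the cluster-adjusted 3.18, because it ignores clustering. That is a separate problem. The precision figures above compare the cluster-adjusted SE with and without the covariate.

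**Conclusion.** The point holds in a limited form. The protocol names unadjusted t tests as its inferential comparison, uses the baseline score for significance tests between groups, and nowhere names it as a covariate. This is an inefficient choice, not a validity error.

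The size is uncertain. The variance reduction runs from about 5% (r = 0.3, within-unit only) to 36% (r = 0.6 at both levels), and at the low end the SE moves by less than 0.1 point against a 10-point target. Every figure rests on an SD of 20 inferred from n = 84, about 13 to 14 units inferred from 394/30, the planning ICC of 0.03, and an assumed r. The power gains depend further on how r splits between levels and on the reference distribution; with so few units the t-based figures are the safer reading. What does not depend on r is that the baseline tests serve no purpose and that the covariate costs nothing to add.

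**What to change.** In the Statistical analysis section:
- Make the two-level mixed model (residents within teaching units) the primary analysis of the 1-month score, with the resident's baseline competence score as a fixed covariate, together with the training variables promised in the Discussion.
- Use the same model for the 6-month score, in place of the unadjusted t tests.
- Report baseline characteristics and scores by group descriptively, and delete the baseline significance tests in items 1 and 2.

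The cost is a few sentences of protocol text. All the variables are already in the data collection plan, and the sample size need not change.
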